##### Nonresponse to treatment

Nonresponse will be defined as persistent symptoms, a sustained titer of CSF-VDRL/RPR (i.e., the titer did not decrease by two dilutions or showed reversion to nonreactivity), or an elevated CSF-WBC count during the 12-month follow-up.

##### Recurrence of neurosyphilis

Recurrence will be defined as recurrent symptoms or a CSF-VDRL/RPR titer or CSF-WBC count that becomes negative or normal after treatment but subsequently reverts to reactive or abnormal during the 12-month follow-up period.

##### Time to recovery

Time to recovery will be defined as the time to achieve an “overall response” after treatment.

##### Withdrawal

Withdrawal will be defined as any withdrawal for any reason of an individual from this trial during the 12-month follow-up period.

### Sample size

Sample size will be calculated as described [24]. A useful approximate formula is:$$D={\left(1+R\right)}^2/{\left(1-R\right)}^2\times f\left(\upalpha, \upbeta \right)$$

where *R* is defined as the hazard ratio or risk ratio (RR) and *f*(*α*, *β*) = (*Z*_*β*_ + *Z*_*α*/2_)^2^ equals 7.85 for 80% power, with α = 0.05 and where *Z* is a standardized normal deviation. The RR has been reported to be 1.5 for serological cure (i.e., a two-dilution decrease in CSF-VDRL titer or reversion to nonreactivity) of neurosyphilis treated with ceftriaxone and ACPG [14]. This calculation showed that 196 primary events are required. A recent retrospective study reported that the rates of serological responses in patients treated with ACPG and ceftriaxone were 82% and 88%, respectively [12]. Based on an expected rate of successful treatment of 85%, 230 participants will be recruited. Because rates of loss to follow-up in such clinical trials have not been reported, the loss to follow-up rate in the present trial was set at no more than 20% [25] to ensure the quality of this trial. Thus, a total of 290 patients will be recruited, with 58 at each study center.

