## Methods

### Study design

This prospective, multicenter, non-inferiority, randomized, controlled trial was designed to compare the efficacy of ACPG and ceftriaxone in the treatment of patients with neurosyphilis. Patients will be randomized 1:1 to treatment with ACPG or ceftriaxone. Clinical data will be recorded prior to treatment and 3, 6, 9, and 12 months after treatment. The flow diagram of this trial is shown in Fig. 1 and its schedule is shown in Fig. 2. This trial was designed in accordance with the World Health Organization (WHO) Trial Registration Data Set (TRDS) and all relevant items are present in this protocol.

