### Statistical analysis

All statistical analyses will be performed using SPSS 21.0 statistical software by biostatisticians blinded to group assignment. Missing data for the primary outcome will be imputed using the multiple imputation method. Serum and CSF RPR titers will be analyzed after log_2_ conversion. Normally distributed continuous variables in the two groups will be compared by *t* tests, and categorical variables will be compared by the *χ*^2^ test or *Fisher’s *exact test, as appropriate. Nonparametric variables will be compared by rank sum tests. The correlation between serum and CSF RPR titers will be analyzed using Spearman’s rank correlation tests. Based on the assumption that there are no obvious correlations between primary outcomes and that it will be impossible to determine which outcome has greater weight, the weights of these primary outcomes will be evaluated using the “Experts Scores” algorithm, with “overall response” to treatment evaluated according to the total efficacy scores from these primary outcomes. The results of each primary outcome will also be evaluated separately. The non-inferiority margin will be set at 10 percentage points for the absolute difference between the two groups. If the standard for non-inferiority is reached, all primary and secondary outcomes will be tested for superiority (*P*<0.05). Non-inferiority will be considered reached if conclusions drawn from the intention-to-treat (ITT) population, consisting of all patients who met the inclusion criteria, were randomized, and started treatment, and the per-protocol population, consisting of all patients with good compliance and who followed the protocol to completion of the treatment regimen, are consistent. Univariate analyses will be performed to identify potential factors associated with the treatment outcome, with variables having a *P* value ≤0.10 in univariate analyses included in a multivariate logistic regression model. Odds ratios (ORs), adjusted ORs (aORs), and their 95% confidence intervals (CIs) will be calculated. A two-sided *P value* <0.05 will be considered statistically significant. Because the efficacy and safety of ceftriaxone and ACPG are clear and both are recommended by Chinese National Guidelines, this trial will not include interim analyses.

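### The 290-patient sample size comes from a formula for detecting a ratio of 1.5; for the planned 10-point non-inferiority test it gives about 57% power, not 80%, if both drugs have an 85% response

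*Protocol article*

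**What the plan says.** The Study design section sets the question: "This prospective, multicenter, non-inferiority, randomized, controlled trial was designed to compare the efficacy of ACPG and ceftriaxone". The Statistical analysis section fixes the criterion: "The non-inferiority margin will be set at 10 percentage points for the absolute difference between the two groups". The only significance level it gives is a general one: "A two-sided *P value* <0.05 will be considered statistically significant".

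The Sample size section takes another route. It uses D = (1+R)²/(1−R)² × f(α, β), where f "equals 7.85 for 80% power, with α = 0.05". The input for R is a published ratio: "The RR has been reported to be 1.5 for serological cure". The result follows: "This calculation showed that 196 primary events are required". The section then cites a retrospective study in which "the rates of serological responses in patients treated with ACPG and ceftriaxone were 82% and 88%, respectively", and continues: "Based on an expected rate of successful treatment of 85%, 230 participants will be recruited". A 20% allowance for loss to follow-up brings the total to 290, or 58 at each of five centers.

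**The concern.** The formula gives the number of events needed to detect that one arm does better than the other by a ratio of 1.5. A non-inferiority sample size depends on the margin, and the 10-point margin appears nowhere in this calculation. The 80% power therefore does not describe the test that answers the trial's question, and the article gives no power for that test.

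The inputs also do not fit together. A ratio of 1.5 sits beside response rates of 82% and 88%, whose ratio is close to 1.

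The trial is meant to inform national treatment guidelines. If the two drugs are equally good and power is well below 80%, a failure to show non-inferiority is a likely result, and readers could take it as evidence against ceftriaxone.

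**Working it through.** **Reproducing the plan's figures** (all inputs from the Sample size section)

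- Events: (1 + 1.5)²/(1 − 1.5)² × 7.85 = 25 × 7.85 = 196.25, stated as 196.
- Evaluable patients: 196/0.85 = 230.6, stated as 230.
- Recruited: 230/0.80 = 287.5, raised to 290 = 5 × 58.

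There is no slip in the arithmetic. The problem is which question the formula answers.

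**Consistency of the inputs**

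- The cited rates give 0.88/0.82 = 1.07, not 1.5.
- A risk ratio of 1.5 on an ACPG rate of 82% implies 1.5 × 82% = 123%.
- A risk ratio of 1.5 around a mean of 85% implies 68% and 102%.

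The last two are impossible as proportions.

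**Power of the non-inferiority test**

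Inputs:

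- Margin 0.10 (Statistical analysis).
- Rate 85% in both arms. The 85% is from Sample size; equality of the arms is an assumption.
- 115 per arm, from 230 evaluable at 1:1.
- z = 1.96. This is the Z for α/2 in the sizing formula and matches the two-sided 0.05 rule. No separate level is stated for the non-inferiority bound.

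Power = Φ[(margin − (p_ACPG − p_ceftriaxone))/SE − z], with SE = √[p_ACPG(1 − p_ACPG)/n + p_ceftriaxone(1 − p_ceftriaxone)/n].

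- SE = √(2 × 0.85 × 0.15/115) = √(0.255/115) = 0.0471.
- Power = Φ(0.10/0.0471 − 1.96) = Φ(0.164) = 56.5%.

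Exact binomial enumeration agrees: 57.5% with a Wald bound and 55.7% with a Newcombe bound. Taking 290 less 20% as 116 per arm gives 56.9%.

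| True rates, ACPG / ceftriaxone | Per arm | One-sided level | Power |
|---|---|---|---|
| 85% / 85% | 115 | 2.5% | 56.5% |
| 85% / 85% | 145 (all 290) | 2.5% | 66.4% |
| 85% / 85% | 115 | 5% | 68.4% |
| 85% / 85% | 145 (all 290) | 5% | 77.0% |
| 82% / 82% | 115 | 2.5% | 50.6% |
| 88% / 88% | 115 | 2.5% | 64.6% |
| 88% / 88% | 145 (all 290) | 5% | 83.5% |
| 85% / 83% | 115 | 2.5% | 38% |
| 82% / 88% | 115 | 2.5% | 92.7% |

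**Size needed for 80% power at 85% in both arms**

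- One-sided 2.5%: n per arm = 7.85 × 0.255/0.10² = 200.2, so 201. That is 402 evaluable, and 402/0.80 = 502.5, so 503 recruited.
- One-sided 5%: 158 per arm, 316 evaluable, 395 recruited.

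**Margin that 115 per arm supports at 80% power**

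(1.96 + 0.84) × 0.0471 = 0.132, or 13.2 points.

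**The case against.** The strongest reply is that the plan never says both arms respond at 85%. It uses that figure only to turn events into patients. The arm-specific rates it cites favor ceftriaxone, and under them non-inferiority power is about 93%. This is true. However, the plan does not name a 6-point advantage as its planning assumption, and a non-inferiority trial should not depend on such an advantage without saying so.

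Second, 57% also depends on a one-sided 2.5% level and on 230 evaluable patients. No confidence level is stated for the non-inferiority bound. Missing primary outcomes are to be imputed, so the intention-to-treat set may come close to 290. This also stands. At 85% in both arms the range is about 57% to 77%, and the top of it treats imputed patients as fully informative. Power with equal rates passes 80% in the table only when both rates are raised to 88%, all 290 count and the level is one-sided 5%.

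Third, the rates are for serological response. The plan also forms an expert-weighted overall response and gives no rate for it, so its power cannot be computed. The figures here are for one binary outcome.

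Fourth, the formula allows R to be a hazard ratio, and a hazard ratio of 1.5 is compatible with a mean of 85% (about 79% and 91% under proportional hazards). The impossibility argument therefore holds only for a risk ratio. That is how the Abbreviations list defines RR, and the published value is given for a cure proportion. Read as a hazard ratio, 82% and 88% would still give only ln(0.12)/ln(0.18) = 1.24. On either reading, the margin is absent from the calculation.

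**Conclusion.** The concern holds. The calculation is carried out correctly, but it sizes a test for detecting a ratio of 1.5, and the 80% power cannot be carried over to the 10-point non-inferiority test.

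For one binary response outcome with 85% in both arms, 230 evaluable patients and a one-sided 2.5% level, power is about 57%: only a little better than even odds when the drugs are equally effective. More generous readings of the level and the analyzed number raise it to at most 77% at those rates. It falls to 38% if ceftriaxone is 2 points worse, and reaches about 93% only if ceftriaxone is 6 points better. The requirement that the intention-to-treat and per-protocol conclusions agree cannot raise any of these figures. The limitations in the Discussion do not mention power. This should be corrected before the results are interpreted.

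**What to change.** In the Sample size section, remove the calculation based on a ratio of 1.5 and 196 events. Replace it with the non-inferiority formula for two proportions, naming the outcome, the rate in each arm, the 10-point margin and the level of the confidence bound.

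Keep the 290 and restate its power. With 230 evaluable and one-sided 2.5%, it is about 57% if both rates are 85%, about 93% at 82% and 88%, and 38% if ceftriaxone is 2 points worse (85% and 83%). If the sponsor relies on ceftriaxone being truly better, that should be stated as the planning assumption. Add to the analysis section or the limitations that failing to show non-inferiority is not evidence of inferiority.

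The cost is a change of wording in the protocol and the analysis plan, and a less favorable stated power. Recruitment, treatment and data collection are unaffected.

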### Randomization

Block randomization will be used in the trial. Patients newly diagnosed with neurosyphilis will be randomly assigned 1:1 to the ACPG or ceftriaxone group. The randomization codes will be produced by an independent statistician at the head research center who was unaffiliated with this trial using PROC PLAN through SAS 9.2 software. Each sub-center will be assigned 58 block sequences, and the randomization schedule will be managed by independent investigators not involved in the implementation or statistical analysis of this study.

### Blinding

Because of the obvious differences between modes of administration of ACPG and ceftriaxone, both patients and clinicians will be aware of their group assignment, precluding the possibility of a double-blind study design. However, the outcome assessors and data analysts can be masked (blinded) to the treatment assignment. This prospective randomized open-blinded endpoint (PROBE) study design is frequently used to improve the reliability of analytic results [26].

### Management of data and biological samples

Each research center should assign investigators to collect clinical information from patients, including demographic characteristics (patient name, ID number, telephone number, and other identifying information, which will be kept anonymously), history of sexually transmitted disease (STD) infection and treatment, lifestyle, information acquired at each visit (including clinical manifestations, results of laboratory tests and auxiliary examinations, and diagnosis and treatment information), and the occurrence and management of adverse events. All adverse event data will be systematically collected using standardized coding MedDRA, with the details recorded in a case report form (CRF). At each research center, several researchers will be assigned to call the enrolled patients to remind them of each follow-up visit. Real-time telephone consultations and psychological counseling can be provided after treatment to improve follow-up compliance. All data on each patient will be double entered into an electronic CRF (eCRF). Data from patients who did not complete follow-up and voluntarily withdrew from the study will be retained with other data.

At the end of the trial, the investigators at each branch center will submit the eCRFs of all patients to the head research center. Information on the eCRF for each patient should be complete and signed. All data will be submitted to the Data Monitoring Committee (DMC) of the head research center and uploaded to the Resman Clinical Trial Management Public Platform (http://www.medresman.org.cn/pub/cn/proj/search.aspx) within 6 months after completion of the trial. The results of the trial will be published in a peer-reviewed journal. Documents of all participants will be preserved for at least 10 years after publication, allowing the original data to be accessed if necessary. The clinical data will be used in future studies with the consent of the participants.

The specimens (blood and CSF) used in this trial will be collected by hospital laboratory staff for diagnosis and assessment of the clinical efficacy of treatments for neurosyphilis. After analysis, the samples will be destroyed and will not be kept for future studies.

### Quality control

The head research center is the Institute of Dermatology, Chinese Academy of Medical Science, which has created a standardized operating procedure (SOP) for clinical research to ensure that the treatment protocol is followed throughout the clinical study. Prespecified SOPs for interventions, details about filling out the CRF, result evaluation, and data management will be used to train-related staff members. In addition, quality controllers at each branch center will control the quality of the research tasks performed by each branch center twice per year, such as the implementation of the study protocol, the intervention of the subjects, the completion of the informed consent documents, the filling out of CRF, and the recording and reporting of adverse events. Furthermore, the inspector from the DMC of the head research center will monitor the trial process and the data from each branch research center once per year. If problems are found, the branch research center will be rectified and assessed in strict accordance with the relevant standard operating requirements of this trial. The trial will continue after the branch research center passes the assessment.

### Statistical analysis

All statistical analyses will be performed using SPSS 21.0 statistical software by biostatisticians blinded to group assignment. Missing data for the primary outcome will be imputed using the multiple imputation method. Serum and CSF RPR titers will be analyzed after log_2_ conversion. Normally distributed continuous variables in the two groups will be compared by *t* tests, and categorical variables will be compared by the *χ*^2^ test or *Fisher’s *exact test, as appropriate. Nonparametric variables will be compared by rank sum tests. The correlation between serum and CSF RPR titers will be analyzed using Spearman’s rank correlation tests. Based on the assumption that there are no obvious correlations between primary outcomes and that it will be impossible to determine which outcome has greater weight, the weights of these primary outcomes will be evaluated using the “Experts Scores” algorithm, with “overall response” to treatment evaluated according to the total efficacy scores from these primary outcomes. The results of each primary outcome will also be evaluated separately. The non-inferiority margin will be set at 10 percentage points for the absolute difference between the two groups. If the standard for non-inferiority is reached, all primary and secondary outcomes will be tested for superiority (*P*<0.05). Non-inferiority will be considered reached if conclusions drawn from the intention-to-treat (ITT) population, consisting of all patients who met the inclusion criteria, were randomized, and started treatment, and the per-protocol population, consisting of all patients with good compliance and who followed the protocol to completion of the treatment regimen, are consistent. Univariate analyses will be performed to identify potential factors associated with the treatment outcome, with variables having a *P* value ≤0.10 in univariate analyses included in a multivariate logistic regression model. Odds ratios (ORs), adjusted ORs (aORs), and their 95% confidence intervals (CIs) will be calculated. A two-sided *P value* <0.05 will be considered statistically significant. Because the efficacy and safety of ceftriaxone and ACPG are clear and both are recommended by Chinese National Guidelines, this trial will not include interim analyses.

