**Exclusion criteria**	
1. Allergy to aqueous crystalline penicillin G or ceftriaxone	
2. Exclusion from other central nervous system diseases or conditions that might cause abnormalities in cerebrospinal fluid tests	
3. Pregnancy and lactation	
4. Serious adverse reactions during treatment	
5. Standardized treatment not carried out strictly according to the treatment regimen, or inability to follow up as required	
6. Patients who require the termination of treatment, for which the efficacy and adverse reactions cannot be evaluated, or patients who request withdrawal from the study	
7. Patients with incomplete clinical data that cannot be counted	

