#### Ceftriaxone group

Patients in the ceftriaxone group will be treated IV with 2 g ceftriaxone per day for 10–14 days, followed by intramuscular injections of benzathine penicillin, 2.4 million U per week, for 3 weeks, in accordance with previous guidelines [6, 16].

Prior to treatment with ACPG or ceftriaxone, patients will be treated with glucocorticoids to prevent the occurrence of adverse reactions, such as Jarisch–Herxheimer reaction (JHR), as determined by clinicians. Patients with worsening mental disorders or severe adverse events due to treatment were allowed to discontinue treatment. After treatment, patients will be followed up every 3 months for the first year, with clinicians informing patients of return visits by telephone.

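### One unqualified imputation rule covers all missing primary outcomes: exits for worsening or severe adverse events have no stated scoring, and Table 1 conflicts with the ITT set on whether they are kept

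*Protocol article*

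**What the plan says.** All references are to the protocol article.

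- **Statistical analysis**, missing data: "Missing data for the primary outcome will be imputed using the multiple imputation method". No exception is made by reason.
- **Statistical analysis**, populations: the ITT set is described as "consisting of all patients who met the inclusion criteria, were randomized, and started treatment". The per-protocol set is limited to compliant patients who completed the regimen. Non-inferiority (margin 10 percentage points) requires the two conclusions to agree.
- **Interventions, Ceftriaxone group**: "Patients with worsening mental disorders or severe adverse events due to treatment were allowed to discontinue treatment".
- **Improvement of clinical manifestations** (a primary outcome): worsening is one of the categories recorded for each symptom.
- **Withdrawal**: "any withdrawal for any reason of an individual from this trial during the 12-month follow-up period".
- **Nonresponse to treatment** (listed under secondary outcomes): "Nonresponse will be defined as persistent symptoms, a sustained titer of CSF-VDRL/RPR" or a raised CSF white cell count. Stopping for worsening or an adverse event is not named.
- **Table 1, exclusion criteria**: criterion 4 is "Serious adverse reactions during treatment". Criterion 5 covers treatment not given to the regimen. Criterion 6 begins "Patients who require the termination of treatment, for which the efficacy and adverse reactions cannot be evaluated" and adds patients who ask to withdraw.
- **Sample size**: 85% expected success, and "the loss to follow-up rate in the present trial was set at no more than 20" per cent.

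**The concern.** The reason a patient stops can carry information about the outcome. Worsening during treatment is direct evidence on the clinical primary outcome. The decision to stop is made open-label, so its frequency could differ between arms for reasons linked to treatment.

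The visit schedule makes a gap plausible. Treatment takes about two weeks plus three weekly injections. The first scheduled post-baseline assessment is at 3 months, and CSF RPR is measured only at 6 and 12 months. A patient who worsens on treatment and then leaves has no scheduled visit at which the worsening would be scored. Missing-at-random imputation would then borrow from patients who stayed, most of whom are expected to respond.

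If such exits are more frequent on ceftriaxone, imputation shrinks a real deficit and favours non-inferiority. If they are more frequent on ACPG, the comparator is flattered. The requirement that ITT and per-protocol agree does not guard against this. The ITT analysis would impute these patients and the per-protocol analysis would omit them, so both can miss the same failures.

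**Working it through.** **1. The plan's own figures.** Events: (1 + 1.5)² / (1 − 1.5)² × 7.85 = 25 × 7.85 = 196.25, stated as 196. Participants: 196 / 0.85 = 230.6, stated as 230. Allowing 20% loss: 230 / 0.80 = 287.5, hence 288, rounded to 290 = 5 × 58, or 145 per arm. These reproduce and supply the inputs below.

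**2. What happens to a patient who stops for worsening or a severe event and has no later data.**

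- ITT definition plus the imputation sentence: kept and imputed.
- Table 1, criteria 4 to 6, read literally: removed after randomisation.
- Per-protocol definition: omitted.
- Nonresponse definition: does not name the case.

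No route states that the patient counts as a failure, and the first two contradict each other.

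**3. Size of the possible bias.** Inputs from the article: 145 per arm, 85% response, 10-point margin. Assumed: a single binary response, 85% among observed patients in both arms, exits that are true failures with no later data, no other missing data, and an imputation model without predictors of worsening. The exit rates d are also assumed.

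- True difference = 0.85 × (1 − d_ceftriaxone) − 0.85 × (1 − d_ACPG) = −0.85 × (d_ceftriaxone − d_ACPG).
- Expected difference after imputation by arm = 0.85 − 0.85 = 0.

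A 5-point excess of such exits on ceftriaxone therefore hides 0.85 × 5 = 4.25 of the 10 margin points. The excess that hides the whole margin is 10 / 0.85 = 11.8 points.

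**4. Effect on the conclusion.** Simulation of 4,000 trials per row, 20 imputations by arm, Rubin's rules, lower 95% bound compared with −10 points:

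| Exits, ACPG | Exits, ceftriaxone | True difference (points) | Non-inferior, imputed | Non-inferior, counted as failures |
|---|---|---|---|---|
| 5% | 5% | 0 | 63% | 57% |
| 3% | 6% | −2.55 | 65% | 38% |
| 5% | 10% | −4.25 | 63% | 22% |
| 5% | 15% | −8.5 | 63% | 5% |
| 5% | 16.8% | −10 | 61% | 2.7% |

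**5. Closed-form check of the 5% v 10% row, exits counted as failures.** Response is 0.85 × 0.95 = 0.8075 on ACPG and 0.85 × 0.90 = 0.765 on ceftriaxone. SE = √[(0.8075 × 0.1925 + 0.765 × 0.235) / 145] = 0.0481. Probability = Φ[(0.10 − 0.0425) / 0.0481 − 1.96] = Φ(−0.76) = 0.22, as simulated. For 85% v 85% with complete data, SE = √(2 × 0.85 × 0.15 / 145) = 0.0419 and Φ(0.10 / 0.0419 − 1.96) = 0.66. The 61% to 65% in the imputation column is this figure less a small loss from imputation. What matters here is the gap between the last two columns, not the level.

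**The case against.** The case against has several strong parts, and most of them limit the point.

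- **The imputation model is not shown.** A reader might infer that known failures will mostly be imputed as responders. The article does not say so. It records manifestations and laboratory results at each visit, and adverse events, so a model could use them. The details may sit in an analysis plan that is not at hand. This stands, with one reservation: if few patients who stop for worsening have later data, the model has few cases from which to learn their lower response.
- **Stopping treatment is not a missing outcome.** Such patients may still be seen at 3 to 12 months, and worsening recorded then is observed data. This stands. The problem needs a second step, absence of later assessment, whose frequency is not given.
- **Table 1 may remove these patients.** This also stands. It replaces one problem with another, because removal after randomisation contradicts the ITT definition and still does not count the failure.
- **The outcomes differ.** Mental worsening bears on the clinical outcome. It does not establish failure of the CSF white cell count or of CSF or serum RPR. The 85% follows cited serological response rates of 82% and 88%, so applying it to clinical response is an assumption.
- **A severe adverse event is not an efficacy failure.** Making it non-response on every primary outcome in the main analysis is a choice of estimand, not a correction. This stands.
- **The exit rates are invented.** They are. The 20% is a ceiling on loss for any reason, and with equal exits the effect is modest.

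A reader might also extend the point to deaths. The passages on stopping and withdrawal do not mention death, so it is left out.

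**Conclusion.** The point holds in limited form. The article fixes one unqualified imputation rule while foreseeing exits that are informative about a primary outcome. It states no scoring for them, and it contradicts itself on whether they are analysed or removed. The second required analysis does not close the gap.

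The size is conditional. The bias is about 0.85 times the between-arm difference in failure-related exits without later data. At an assumed 5% v 10% it moves the chance of declaring non-inferiority from about 22% to about 63%. At an assumed 5% in both arms it moves from 57% to 63%. These figures rest on assumed exit rates, exits being true failures, and a model that cannot recognise them. They show what the rule could do, not what it will do.

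**What to change.** 1. Reconcile Table 1 (criteria 4 to 6), the discontinuation sentence under Interventions and the Statistical analysis section, so that patients who started treatment stay in the ITT set. This concerns who is analysed and how they are scored. It changes no rule on when treatment may stop.
2. Use any later assessments of patients who stop treatment. Where there are none, score documented clinical worsening as failure of the clinical-manifestation outcome and of the overall response.
3. Keep multiple imputation, run by arm, for other missing primary data.
4. Require the non-inferiority conclusion to be checked by two sensitivity analyses: one counting exits for worsening or severe treatment-related events as non-response, and a tipping-point analysis that lowers the imputed ceftriaxone response until non-inferiority is lost.

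The cost is some wording and one or two extra analyses. The reason for stopping treatment must be available separately from the reason for leaving the trial. Reported response rates may be slightly lower.

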### Outcomes

All parameters will be assessed at baseline before treatment (T0) and at follow-up timepoints 3 (T1), 6 (T2), 9 (T3), and 12 (T4) months later.

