#### Secondary outcomes

##### MMSE score

General paresis is the most frequently reported clinical presentation of neurosyphilis in China [17], with patients having different levels of cognitive impairment. The Mini-Mental State Examination (MMSE), one of the earliest and most widely used brief cognitive assessment tools [18], is utilized to evaluate the severity of dementia among patients with general paresis [19]. In this study, MMSE scores will be determined before treatment and at each follow-up to determine the degree of recovery from cognitive impairment among patients presenting with general paresis at baseline.

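### MMSE is scored at five visits, but the only comparisons named for it are single-time two-group tests, which set aside earlier scores and are open to bias if loss is related to decline and unequal between arms

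*Protocol article*

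**What the plan says.** All from the protocol article.

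- **Outcomes:** parameters are assessed at baseline and "at follow-up timepoints 3 (T1), 6 (T2), 9 (T3), and 12 (T4) months later".
- **MMSE score** (a secondary outcome): "MMSE scores will be determined before treatment and at each follow-up to determine the degree of recovery from cognitive impairment", and this is done "among patients presenting with general paresis at baseline". The size of that subgroup is not given.
- **Statistical analysis, tests:** "Normally distributed continuous variables in the two groups will be compared by" t tests; "Nonparametric variables will be compared by rank sum tests". No repeated-measures method is named.
- **Statistical analysis, missing data:** "Missing data for the primary outcome will be imputed using the multiple imputation method". Nothing is said either way about secondary outcomes.
- **Statistical analysis, use of the result:** once non-inferiority is reached, secondary outcomes are tested for superiority at two-sided 0.05.
- **Sample size and Discussion:** loss to follow-up is set at no more than 20%, and loss is expected to grow with time.
- **Management of data and biological samples:** data from patients who withdraw are kept.

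**The concern.** A t test or rank sum test compares two groups at one time. Applied at month 12, it can include only patients who have a month-12 score. What the others scored at months 3, 6 and 9 plays no part, although those scores have been collected and kept. A test on the raw score also ignores baseline MMSE. A test on change would use baseline only by subtraction.

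In general paresis the patients who are declining may be the harder ones to bring back. If that happens to a different degree in the two arms, the arm that loses more of them looks better than it is. The trial is open-label, and the Discussion says the penicillin regimen is burdensome and that many patients prefer ceftriaxone, so unequal retention cannot be ruled out. At stake is a superiority statement on cognition, which the Discussion presents as part of the efficacy evaluation.

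**Working it through.** **The plan's own figures.** No figure is stated for MMSE. The sample size does reproduce. With R = 1.5, (1 + R)²/(1 − R)² = 25 and 25 × 7.85 = 196.25 events. Then 196/0.85 = 230.6 and 230/0.80 = 287.5, taken up to 290 = 5 × 58. None of this changes.

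**Size of the possible bias.** All MMSE inputs are assumptions, because the protocol gives none:

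- baseline mean 18, SD 6;
- mean 12-month gain 3 points, between-patient SD of the gain 4, linear over time;
- visit error SD 2;
- scores treated as normal and unbounded;
- loss placed at the month-12 visit;
- both arms truly equal.

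A patient is lost when a propensity score falls in the lowest fraction p of the arm. The score is the standardised change plus independent noise of equal variance. Two mechanisms were used: loss driven by the change seen up to month 9 (missing at random), and loss driven by the unseen change at month 12 (not at random).

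*Formula.* The completers' mean change is too high by ρ × SD × h(p), with h(p) = φ(z_p)/(1 − p). The bias in the comparison is ρ × SD × [h(p₂) − h(p₁)].

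- SD of month-12 change: √(4² + 2² + 2²) = √24 = 4.90.
- Loss on unseen change: ρ = 1/√2 = 0.707, so ρ × SD = 3.46.
- Loss on month-9 change: variance 0.75² × 16 + 8 = 17 and covariance with month-12 change 0.75 × 16 + 4 = 16. The correlation is 16/(4.90 × 4.12) = 0.792. So ρ = 0.792 × 0.707 = 0.560 and ρ × SD = 2.74.
- h(0.10) = 0.195, h(0.15) = 0.274, h(0.20) = 0.350, h(0.25) = 0.424, h(0.30) = 0.497.

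| Loss by arm (mean 20%) | Bias, loss at random given observed scores | Bias, loss not at random |
|---|---|---|
| 20% / 20% | 0 | 0 |
| 15% / 25% | 2.74 × 0.149 = 0.41 | 3.46 × 0.149 = 0.52 |
| 10% / 30% | 2.74 × 0.302 = 0.83 | 3.46 × 0.302 = 1.04 |

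A simulation with 200,000 patients per arm printed completer differences of 0.40 and 0.50 for the middle row and 0.81 and 1.00 for the last. When loss was unrelated to MMSE, the bias was about 0 at every split.

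**What using all visits does.** In the same simulation month-12 scores were predicted, arm by arm, from the four earlier visits, as a stand-in for a repeated-measures model. The bias was about 0 when loss depended on observed scores. When loss depended on unseen change, about 0.2 points remained at 15%/25% and about 0.4 at 10%/30%.

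**Against sampling error.** The subgroup size is unknown, so take 30 to 116 month-12 scores per arm; 116 is 145 × 0.8, every randomised patient less 20%. The standard error of the difference is 4.90 × √(2/n), that is 1.26 to 0.64 points. A bias of 0.4 to 0.5 is roughly 0.3 to 0.8 of a standard error.

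**The case against.** The strongest reply is that this is a condensed article, and that missing-data handling for a secondary outcome in one subtype belongs in the statistical analysis plan. Much of that stands. A reader might infer that imputation is reserved for the primary outcome, that MMSE will be analysed in completers only, or that four separate visit-wise tests are planned. The text says none of these; it is silent, and it keeps withdrawn patients' data. What survives is that the article does name the tests for continuous variables, and those tests do not suit a score measured five times.

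A reader might also take "Patients with worsening mental disorders or severe adverse events due to treatment were allowed to discontinue treatment" as the route by which declining patients vanish from the MMSE comparison. The sentence concerns stopping treatment, not leaving follow-up. Treatment is at most 14 days plus three weekly injections, so it ends about five weeks in, before the first follow-up MMSE at month 3. Table 1 does list post-enrolment events among its exclusions, including inability to follow up and incomplete data, which leaves some room for selective removal. But no passage ties loss to MMSE decline or to arm, and reminder calls go to all enrolled patients.

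It is tempting to say that the named test will flatter one arm. That needs both conditions at once: loss related to decline, and loss that differs between arms. Larger biases than 0.4 to 0.5 points need a more uneven split, or overall loss above the 20% the protocol sets as its limit.

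**Conclusion.** The point holds as a modest improvement to a stated method. The named tests leave collected information unused and give no protection if loss is informative and unequal. On the assumed inputs the bias at month 12 is about 0 at 20%/20% loss, about 0.4 to 0.5 points at 15%/25%, and about 0.8 to 1.0 at the more extreme 10%/30%. These figures scale with the assumed SD and with how strongly loss follows decline. The protocol supports neither a particular split nor a particular mechanism, so they show a possible size and are not a forecast.

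A reader might infer that the trial's main answer is at risk. It is not: MMSE is secondary, is confined to general paresis, does not enter the overall response built from the primary outcomes, and is tested for superiority only after non-inferiority is reached.

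**What to change.** For MMSE, replace the t or rank sum test with one mixed model for repeated measures. It should use all follow-up scores of general-paresis patients in the intention-to-treat population, with terms for arm, visit, arm-by-visit and baseline MMSE. State that the month-12 contrast is the deciding result. Add one sensitivity analysis that gives unfavourable values to patients who leave because of mental worsening, since the model alone does not remove bias when loss depends on unseen scores.

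The cost is a few lines of analysis text and a little programming, with no new data, visits or patients. The drawback is reliance on a missing-at-random assumption, which the sensitivity analysis probes. The change should be confined to MMSE. Serum RPR response is a primary outcome with a binary cure definition and already falls under the stated imputation.
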